# Radiation-induced toxicity after image-guided and intensity-modulated radiotherapy versus external beam radiotherapy for patients with spinal bone metastases (IRON-1): a study protocol for a randomized controlled pilot trial

**DOI:** 10.1186/s13063-017-1847-1

**Published:** 2017-03-03

**Keywords:** Spinal bone metastases, Intensity-modulated radiotherapy, Palliative radiotherapy, Toxicity

## Abstract

**Background:**

Radiation therapy (RT) of bone metastases provides an important treatment approach in palliative care treatment concepts. As a consequence of treatment, the extent of radiation-induced toxicity is a crucial feature with consequences to a patient’s quality of life. In this context this study aims at reducing the extent of radiation-induced side effects and toxicity by assuming a better sparing of normal tissue with the use of intensity-modulated instead of conventionally delivered external beam radiotherapy.

**Methods/design:**

In this prospective, randomized, single-center trial for patients with spinal bone metastases, RT is performed as either image-guided intensity-modulated radiotherapy (10x3Gy) or conventionally fractionated external beam radiotherapy (10x3Gy). Afterwards radiation-induced toxicity will be assessed and compared 3 and 6 months after the end of radiation.

**Discussion:**

The aim of this pilot study is the evaluation of achievable benefits, with reduced radiation toxicity being the primary endpoint in the comparison of intensity-modulated radiotherapy versus conventional radiotherapy for patients with spinal bone metastases. Secondarily, bone re-calcification, quality of life, pain relief, spinal instability, and local control will be measured and compared between the two treatment groups.

**Trial registration:**

ClinicalTrials.gov, NCT02832830. Registered on 12 July 2016.

**Electronic supplementary material:**

The online version of this article (doi:10.1186/s13063-017-1847-1) contains supplementary material, which is available to authorized users.

## Background

Secondary bone metastases in patients with cancer are most often located in the vertebral spine [1–4], leading to complications such as bone fractures, neurological impairment, and especially pain [5–10]. Radiation therapy of bone metastases as a palliative oncological treatment concept is supposed to prevent and treat symptoms such as fatigue and pain. As a consequence of treatment, the extent of radiation-induced toxicity should be kept as low as possible, as it may also immensely reduce the patients’ quality of life.

Conventionally fractionated external beam radiotherapy is one of the most important radiotherapeutic treatment options for spinal bone metastases, delivering common doses of 30 Gy and resulting in a significant decrease in pain [11]. Nevertheless, the use of this technique is limited due to unsatisfactory sparing of surrounding normal tissue as well as application of high doses to organs at risk such as the spinal cord. As the spinal cord is centrally localized within the vertebral body and thus in the target volume, even modern techniques will never be able to completely spare this at-risk organ. However, every reduction of the dose delivered to nearby tissue still can lead to a decrease of side effects and thus a higher quality of life. The use of intensity-modulated radiotherapy aims to better spare the surrounding tissue, leading to a reduction of possible radiation-induced side effects [12]. Image,guidance additionally matches the patient’s positioning to the treatment field and thus improves the accuracy of dose distribution [13].

Considering the extent of radiation-induced acute and late side effects as well as toxicity with its contribution to reduced quality of life, this randomized study compares the quantitative amount of toxicity by using the two above-mentioned radiotherapeutic treatment concepts.

## Methods/design

### Recruitment and study design

This prospective, single-center pilot study is performed at the Department of Radiation Oncology at the University Hospital of Heidelberg for patients with spinal bone metastases with indication for radiotherapy. As shown in Fig. 1, participants will be randomized into two groups: one group receiving intensity-modulated radiotherapy treatment (group A) and the other conventional external beam radiotherapy (group B).

**Fig. 1 Fig1:**
[figure not shown]
Timeline for IRON-1. *RT* radiotherapy, *IMRT* intensity-modulated radiotherapy

The Standard Protocol Items: Recommendations for Interventional Trials (SPIRIT) 2013 checklist shows the study guidelines in more detail (see Additional file 1).

Before the start of radiotherapy, the recruitment of eligible participants firstly includes the explanation, to each potential study participant, of the purpose, implementation, design, aims, requirements, and timeline of this study as well as the description of the two different radiation techniques and common ethical issues.

### Inclusion criteria

Patients will be included who:Have metastases in the vertebral spine, regardless of number of metastasesHave an indication for radiation therapy, such as bone pain, spinal instability, and neurological deficitAre aged 18 to 85Have Karnofsky performance status ≥50Have signed a Declaration of Informed Consent

### Exclusion criteria

Patients will be excluded who:Have bony lesions caused by multiple myeloma or lymphomaHave severe neurological and psychiatric impairmentHave undergone previous radiation therapy with overlapping areas

### Drop-out criteria

Criteria that will lead to the drop-out of a patient before completion of this study may be any kind of treatment for medical reasons or impairment that will result in an interruption or early completion of radiotherapy. Furthermore, the patient’s desire to exit the study or withdrawal of consent as well as any unexpected serious adverse event (SAE) occurring during treatment or in follow-up that leads to early completion of the study will result in drop-out.

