### Data collection and follow-up period

During study observation, patient data are collected before the start of radiotherapy treatment (t0), at the end of treatment (t1), and in the follow-up period at scheduled visits in our department at time points of 3 months (t2) as well as 6 months (t3) after completion of treatment (Figs. 1 and 2).

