### Assessment of the primary and secondary endpoints

In this trial, radiation-induced toxicity 3 months after completion ofpalliative radiotherapy will be evaluated as the primary endpoint. Its extent is measured according to criteria delineated by NCI Common Toxicity Criteria for Adverse Events (CTCAE v 4.0).

Secondary endpoints will be bone re-calcification, quality of life, spinal instability and fractures, local control, and clinical symptoms such as fatigue, pain relief, or neurological deficits.

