### Statistical analysis and randomization

This trial is being performed as a pilot study; in the calculation for statistical analysis a total of about 30 patients in each treatment group is considered an appropriate sample size. Due to the explorative character of this study, it is not possible to estimate the total number of cases. However, with a scheduled number of 30 patients per group, it will be possible to detect a standardized mean-value effect (Cohen’s *d*) of 0.8 with a power of 80% and an alpha significance level of 5%. A blocked randomization is used to allocate each participant into group A or B before start of treatment. All variables were analyzed descriptively by tabulation of the measures of the empirical distributions. According to the scale level of the variables, means, standard deviations, and medians as well as minimum and maximum or absolute and relative frequencies, respectively, will be reported. Additionally, for variables with longitudinal measurements, the time courses of individual patients will be analyzed and summarized by treatment groups. Descriptive *p* values of the corresponding statistical tests comparing the treatment groups will be given. The Wilcoxon signed rank test will be used to compare changes in group difference. The Cohen’s effect size (ES) will be assessed for clinically relevant change in questionnaire measures (<0.3 low, 0.3–0.7 moderate, >0.7 strong difference). Moreover patient data are collected in table form at the above-mentioned time points for all completed questionnaires. All statistical analyses will be performed with SAS software v 9.3 or higher (SAS Institute, Cary, NC, USA).

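### The drop-out rule does not separate stopping radiotherapy from leaving the study, so severe toxicity may be selectively missing at the 3-month primary assessment

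*Protocol article*

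**What the plan says.** The article's Drop-out criteria section lists grounds for leaving the study. Its opening words are "Criteria that will lead to the drop-out of a patient before completion of this study may be", so the exit is from the study and not only from treatment. Three grounds follow:

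- Radiotherapy ground: "any kind of treatment for medical reasons or impairment that will result in an interruption or early completion of radiotherapy". There is no exception for impairment caused by the radiotherapy.
- The patient's own wish to leave, or withdrawal of consent.
- SAE ground: "any unexpected serious adverse event (SAE) occurring during treatment or in follow-up that leads to early completion of the study will result in drop-out".

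Under Assessment of the primary and secondary endpoints, "radiation-induced toxicity 3 months after completion ofpalliative radiotherapy will be evaluated as the primary endpoint". On the scale, the same section says: "Its extent is measured according to criteria delineated by NCI Common Toxicity Criteria for Adverse Events (CTCAE v 4.0". Data collection and follow-up period places the visits after radiotherapy at "time points of 3 months (t2) as well as 6 months (t3) after completion of treatment", with earlier data collection before treatment (t0) and at its end (t1). The primary value is therefore the one obtained at t2.

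**The concern.** Two of the three grounds can be consequences of the outcome, and both can arise before t2. A patient whose radiotherapy is interrupted because of toxicity meets a ground for leaving the trial that is meant to count that toxicity. If that patient has no t2 visit, the primary value is missing for a reason related to what it would have been.

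The trial's rationale is that IMRT causes less toxicity. If that is right, the conventional arm has more patients at risk of leaving this way. The comparison at t2 would then move from all randomised patients towards those who tolerated treatment. Toxicity could be understated in both arms, and the difference between them distorted. An analysis plan can define analysis sets and missing-data methods, but it cannot recover visits that were never made.

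**Working it through.** **Whether the rule can reach the endpoint.** Treatment is 10 fractions at five per week, so 10/5 = 2 weeks. The radiotherapy ground acts in that window, which lies wholly before t2. The SAE ground acts during treatment and follow-up. Events up to t2 can remove the primary value, and events between t2 and t3 cannot.

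**The plan's own figure.** The sample-size statement claims 80% power for Cohen's d = 0.8 at a 5% level "with a scheduled number of 30 patients per group". The article names no test for this, so I assume a two-sided two-sample t-test. The required number is 25.5, so 26 per group, and power at 30 per group is 0.86. The claim is met with a margin. With fewer evaluable patients per group, power is 0.81 at 26, 0.79 at 25, 0.77 at 24 and 0.69 at 20. Losing up to 4 of 30 per group (13%) therefore keeps 80%. The loss of numbers is a minor matter; who is lost is the main one.

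**Illustration 1: binary toxicity, equal exit fractions.** The article gives no rates, so all inputs are assumed: true toxicity p = 20% in conventional radiotherapy (group B) and 10% in IMRT (group A). A fraction s of toxic patients leaves before t2, and no others leave.

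Observed rate = p(1 − s) / (1 − ps)

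For s = 0.25: B = 0.15/0.95 = 15.8%, and A = 0.075/0.975 = 7.7%.
For s = 0.50: B = 0.10/0.90 = 11.1%, and A = 0.05/0.95 = 5.3%.

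| s, both arms | B | A | Difference (points) |
|---|---|---|---|
| 0 | 20.0% | 10.0% | 10.0 |
| 0.10 | 18.4% | 9.1% | 9.3 |
| 0.25 | 15.8% | 7.7% | 8.1 |
| 0.50 | 11.1% | 5.3% | 5.8 |

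**Illustration 2: unequal exit fractions, same true rates.**

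- s = 0.50 in B and 0.25 in A: 11.1% − 7.7% = 3.4 points.
- s = 0.25 in B and 0.50 in A: 15.8% − 5.3% = 10.5 points, slightly more than the true 10.

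The difference can therefore be shrunk or exaggerated.

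**Illustration 3: continuous score, true d = 0.8.** Assume normal scores with equal SD and one severity cut-off for both arms, set at the worst 10%, 20% or 30% of the conventional arm (1.9%, 5.0% or 9.3% of the IMRT arm lie above it). By simulation, starting from 30 per group:

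| Cut-off: worst part of B | Half of those above leave: d, power | All of those above leave: d, power |
|---|---|---|
| 10% | 0.77, 0.82 | 0.73, 0.76 |
| 20% | 0.75, 0.78 | 0.67, 0.66 |
| 30% | 0.73, 0.75 | 0.62, 0.55 |

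With nobody lost, power is 0.86. The effect is modest when only half of the severe cases leave and material when all do.

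**The case against.** A reader might infer that every patient with an SAE is dropped, and that the worst toxicity is therefore removed before it is measured. The text does not support this.

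- **SAE ground.** The SAE must be unexpected and must lead to early completion of the study. By the letter, an expected radiation SAE, or one after which the patient stays in, does not trigger it. To a large extent this ground labels a participation that has already ended.
- **Radiotherapy ground.** Its wording is permissive, and it is not tied to toxicity: disease progression or intercurrent illness fits equally. Treating a side effect while all 10 fractions are delivered drops nobody.
- **Data before exit.** The article does not say they are discarded. Information at t1 may exist, and analysis sets may be settled in a full protocol or SAP that is not shown.
- **Size.** Nothing in the article suggests that half of the toxic patients would leave, and that is probably high for a two-week course.
- **Purpose.** This is an exploratory pilot with descriptive p values.

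All of this stands, and it limits the point to what may be missing. It does not remove it. The opening sentence makes the criteria grounds for leaving the study, and the natural reading is that the permissive words only introduce the list. If they instead grant discretion, someone decides after allocation who leaves, which is no safer. Whatever the analysis plan says about data already collected, a t2 assessment not made stays missing.

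**Conclusion.** The concern holds in a limited form. The drop-out paragraph merges stopping radiotherapy with leaving the study, and some of the triggering events may be the primary outcome itself. Following it can leave 3-month values missing because of toxicity.

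The size is unknown. Under the assumed 20% v 10%, a 10-point difference becomes 9.3, 8.1 or 5.8 points when 10%, 25% or 50% of toxic patients leave in both arms. This assumes that only toxic patients leave, that those who leave would have shown toxicity at 3 months, and that the exit fraction is the same in each arm. Under those conditions toxicity is understated in both arms and the difference shrinks. A reader might conclude that the bias always runs towards no difference and is therefore conservative. That does not follow, because with unequal fractions the direction is uncertain.

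**What to change.** Amend the drop-out paragraph as follows:

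1. Interruption or early end of radiotherapy, or an SAE, does not by itself end follow-up.
2. CTCAE assessments at t1 to t3 continue unless the patient dies or withdraws consent to follow-up.
3. The toxicity that led to any exit is recorded.
4. Patients are compared in the group to which they were randomised.

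Counting toxicity-related exits as toxicity events, or using the worst grade before exit, belongs in a sensitivity analysis. In the primary comparison it would mix acute grades into a 3-month endpoint and score leavers differently from completers.

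The clinical rules for stopping treatment are unchanged. The cost is a short amendment and some follow-up of patients who stopped treatment, at visits already scheduled. The article reports recruitment as incomplete, and an early change protects more of the data.

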### Radiotherapeutic planning and treatment implementation

All patients receive a planning computed tomography (CT) scan with a slice thickness of 3–5 mm. Patient positioning depends on the area being treated and includes the use of various fixation devices, such as Wingstep® and Prostep® (Elekta, Stockholm, Sweden) for lesions in the thoracic or lumbar spine as well as head holders such as Aquaplast masks (Aquaplast Corporation, Wyckoff, NJ, USA) for cervical spine immobilization. In addition to skin tattoo marks, this guarantees the achievement of a high reproducibility of patient positioning and accuracy of treatment delivery.

Afterwards these CT scans are used to outline organs at risk (OARs) and to contour the clinical target volume (CTV), which encompasses the metastatic vertebral body and, with a margin of 1 cm, results in the planning target volume (PTV). The target volume (=PTV) in each treatment group consists of the entire metastatic vertebral body in a craniocaudal direction including the Proc. costales et transversi to the right and left lateral sides.

In group A, treatment is being performed as intensity-modulated radiotherapy (IMRT) and planned as either tomotherapy, volumetric arc therapy (VMAT), or step-and-shoot IMRT with daily cone-beam CT imaging for rigid patient deformation during radiation. In group B radiation is delivered by conventional, three-dimensional (3D) planned, external beam radiotherapy in two to three fields. Each group uses 6 MV photon energy plans with multileaf collimator shaped radiation fields. A palliative treatment regimen with a total prescribed dose of 30 Gy in 3 Gy fraction doses and daily treatment sessions five times per week is performed, with the 90% isodose surrounding the PTV. OARs such as the skin, heart, or the esophagus are delineated, and dose limit constraints are prescribed to each of them following common considerations according to QUANTEC parameters.

### Data collection and follow-up period

During study observation, patient data are collected before the start of radiotherapy treatment (t0), at the end of treatment (t1), and in the follow-up period at scheduled visits in our department at time points of 3 months (t2) as well as 6 months (t3) after completion of treatment (Figs. 1 and 2).

**Fig. 2 Fig2:**
[figure not shown]
Intervention and assessment schedule for IRON-1 trial

Patient clinical information is carefully documented in case report forms (CRFs) using questionnaires, filled out by each patient, that measure and quantify clinical symptoms and factors such as pain, radiation-induced side effects and toxicity, as well as quality of life (European Organisation for Research and Treatment of Cancer Quality of Life Questionnaire for patients with Bone Metastases and for measure of Fatigue (EORTC BM22, FA13) and visual analog scale (VAS)). Furthermore, the follow-up requirements include a CT scan 3 and 6 months after completion of radiotherapy for evaluation of treatment response, bone sclerosis, spinal stability, and possible complications such as bone fractures.

### Assessment of the primary and secondary endpoints

In this trial, radiation-induced toxicity 3 months after completion ofpalliative radiotherapy will be evaluated as the primary endpoint. Its extent is measured according to criteria delineated by NCI Common Toxicity Criteria for Adverse Events (CTCAE v 4.0).

Secondary endpoints will be bone re-calcification, quality of life, spinal instability and fractures, local control, and clinical symptoms such as fatigue, pain relief, or neurological deficits.

### Statistical analysis and randomization

This trial is being performed as a pilot study; in the calculation for statistical analysis a total of about 30 patients in each treatment group is considered an appropriate sample size. Due to the explorative character of this study, it is not possible to estimate the total number of cases. However, with a scheduled number of 30 patients per group, it will be possible to detect a standardized mean-value effect (Cohen’s *d*) of 0.8 with a power of 80% and an alpha significance level of 5%. A blocked randomization is used to allocate each participant into group A or B before start of treatment. All variables were analyzed descriptively by tabulation of the measures of the empirical distributions. According to the scale level of the variables, means, standard deviations, and medians as well as minimum and maximum or absolute and relative frequencies, respectively, will be reported. Additionally, for variables with longitudinal measurements, the time courses of individual patients will be analyzed and summarized by treatment groups. Descriptive *p* values of the corresponding statistical tests comparing the treatment groups will be given. The Wilcoxon signed rank test will be used to compare changes in group difference. The Cohen’s effect size (ES) will be assessed for clinically relevant change in questionnaire measures (<0.3 low, 0.3–0.7 moderate, >0.7 strong difference). Moreover patient data are collected in table form at the above-mentioned time points for all completed questionnaires. All statistical analyses will be performed with SAS software v 9.3 or higher (SAS Institute, Cary, NC, USA).

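### Spinal region enters neither the blocked allocation nor the group comparison described in the article; stratifying the 3-month toxicity comparison by region would be a cheap gain in precision

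*Protocol article*

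**What the plan says.** The Statistical analysis and randomization section describes allocation in one sentence: "A blocked randomization is used to allocate each participant into group A or B before start of treatment". It names no stratification factor. The same section lists descriptive summaries, descriptive p values between treatment groups, a Wilcoxon signed rank test and effect sizes. No stratum or covariate appears. The planned size is justified "with a scheduled number of 30 patients per group" by a standardised effect "of 0.8 with a power of 80% and an alpha significance level of 5" per cent.

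Eligibility is wide. The Inclusion criteria admit "metastases in the vertebral spine, regardless of number of" lesions. The section on radiotherapeutic planning says "Patient positioning depends on the area being treated" and foresees devices "for lesions in the thoracic or lumbar spine" and others "for cervical spine immobilization", so all three regions are expected. On organs at risk it says "OARs such as the skin, heart, or the esophagus are delineated". The primary endpoint is CTCAE v4.0 toxicity 3 months after radiotherapy.

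**The concern.** The Background argues that side effects follow the dose reaching tissue near the target. On that reasoning, what lies next to the treated vertebrae should influence the primary endpoint. The heart and the esophagus, two of the three organs given as examples, adjoin only some spinal levels. Region is therefore a plausible prognostic factor.

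Blocking equalises arm sizes but not case mix. In a trial of 60, the arms may differ by chance in region mix, and the unadjusted difference then carries part of the region effect. A comparison that ignores region also leaves variation in the error term that could be explained.

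Region should be available at baseline. The Exclusion criteria rule out overlapping previous radiotherapy, which cannot be judged without knowing the area to be treated. The number of vertebrae finally treated is less certain, because the article does not place the planning CT before or after allocation.

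**Working it through.** **1. The plan's own figure.** Inputs from the article: 30 per group, d = 0.8, power 80%, alpha 5% (two-sided assumed).
- A two-sample t test (noncentral t) needs 26 per group, with power 80.7%. At 30 per group its power is 86.1%.
- The stated 30 is reproduced if a rank test at its minimum asymptotic relative efficiency of 0.864 is meant: 26 / 0.864 = 30.1 per group, with 80.6% power at 30.
- The t-test figure of 86.1% is the baseline below.

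**2. Chance of imbalance.** The article gives no region mix, so the share is varied. With 60 patients, K of them in the region and 30 per arm, the number X in one arm is hypergeometric (60, K, 30). The imbalance is |2X − K| / 30.

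| Region share (K) | P(at least 20 points) | P(at least 30 points) |
|---|---|---|
| 20% (12) | 0.104 | 0.002 |
| 30% (18) | 0.158 | 0.010 |
| 40% (24) | 0.187 | 0.017 |
| 50% (30) | 0.196 | 0.019 |
| 60% (36) | 0.187 | 0.017 |
| 70% (42) | 0.158 | 0.010 |

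The chance of 20 points or more is thus about 10-20% for a given region. For any of three regions (cervical 10-20%, thoracic 50-70%, lumbar 20-30%, assumed), simulated permutations give 21-32%.

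**3. Size of the shift.** Shift = region effect × imbalance. The region effect is assumed to be 0.3-0.8 SD, and the imbalance is 20 points.
- 0.3 × 0.20 = 0.06 SD; 0.06 / 0.8 = 7.5% of the planned effect.
- 0.8 × 0.20 = 0.16 SD; 0.16 / 0.8 = 20% of the planned effect.

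Given such an imbalance, the type I error of the unadjusted t test is 5.6% (shift 0.06) to 9.4% (shift 0.16). Power at d = 0.8 moves from 86.1% to 80-68% if the shift works against the effect, or to 91-96% if it works with it. Averaged over all allocations, the type I error is not inflated.

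**4. The same on the risk scale.** Assume half of the patients have a cervical or thoracic target, with toxicity 40% in that group and 10% in the lumbar-only group.
- Overall risk 25%; variance 0.25 × 0.75 = 0.1875; SD 0.433.
- Shift at 20 points: 0.20 × (0.40 − 0.10) = 0.06, which is 0.06 / 0.433 = 0.14 SD.
- Target: 0.8 × 0.433 = 0.346, about 35 percentage points.
- Standard error of the difference: √(2 × 0.1875 / 30) = 0.112. The shift is 0.06 / 0.112 = 0.54 standard errors.
- With equal shares, the next possible step above 30 points is 33 (probability 1.9% for that or more). It shifts the result by 0.333 × 0.30 = 0.10.

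**5. Gain from accounting for region.** Between-region variance is 0.5 × 0.5 × 0.30² = 0.0225, and 0.0225 / 0.1875 = 12% of the total. The standard error is multiplied by √(1 − 0.12) = 0.938, about 6% smaller. With region effects of 0.3-0.8 SD and shares of 30-50%, adjustment raises t-test power from 86.1% to about 87-91%.

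**The case against.** The strongest reply is that this is ordinary sampling error. Randomisation makes the unadjusted comparison valid, and its standard error already allows for chance imbalance in every prognostic factor. Unstratified blocking is a common and defensible choice in an exploratory pilot with descriptive p values. This stands: the design is not biased.

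A reader might infer that region imbalance could create or hide the effect the pilot looks for. The figures do not support that. On the illustrative rates, a 20-point imbalance moves the result by 6 points against a target of about 35, and even a 33-point imbalance moves it by 10.

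A reader might also infer that the analysis will certainly ignore region. The article names no adjustment, but it does not rule one out. The full protocol may name strata and the SAP may name covariates; neither is shown.

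It can fairly be added that the article gives no toxicity rate by region and that its organ list is only a set of examples. Calling region one of the strongest predictors would go beyond it. If toxicity is similar across levels, there is little to gain. Finally, one patient may have targets in several regions, so a region factor needs an assignment rule.

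What remains is that the article describes no use of a plausible prognostic factor, available at baseline, in a comparison of 60 patients.

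**Conclusion.** The point holds as a modest improvement, not as a flaw that invalidates the trial. A given region has about a 10-20% chance of an imbalance of 20 points or more. A 20-point imbalance would shift the toxicity difference by 0.06-0.16 SD, 8-20% of d = 0.8. That is enough to blur a pilot estimate that may inform a later trial, but not to produce or mask an effect of that size. The expected gain from stratifying is a standard error about 6% smaller under the illustrative 40% and 10% rates.

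These sizes rest on assumed region shares (20-70%) and assumed region effects (0.3-0.8 SD). That region matters at all is an inference from the protocol's rationale and its organ list. The statement about the analysis is limited to this article.

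**What to change.** Pre-specify, before outcomes are compared, that the 3-month toxicity comparison is stratified by one two-level baseline factor:
- level 1: any cervical or thoracic target, including patients treated in several regions if one of these is among them;
- level 2: lumbar targets only.

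Use a van Elteren test if toxicity is analysed as an ordered grade, or a Mantel-Haenszel risk difference with 95% CI if it is analysed as a proportion. Tabulate toxicity by region and arm, so that any imbalance and its direction are visible.

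The cost is a few sentences of analysis plan and one table. It covers patients already allocated and needs no new data beyond the treated region. The downside is that few events will support only one factor, so further covariates should not be added to the main comparison. The Trial status section says recruitment is not complete, so the blocked list could also be run within the two levels for remaining patients. That is optional, and the stratified analysis does not depend on it.

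### The questionnaire analyses named are of raw change, with no baseline term although t0 is collected; ANCOVA would make this secondary comparison more precise at little cost

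*Protocol article*

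**What the plan says.** All references are to the protocol article.

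- **Data collection and follow-up period.** The article states that "patient data are collected before the start of radiotherapy treatment (t0"), then at the end of treatment (t1) and 3 and 6 months later (t2, t3). The patient-completed instruments are EORTC BM22, EORTC FA13 and a VAS. The statistical section adds that completed questionnaires are tabulated at these time points, so a t0 score should exist for each scale.
- **Assessment of the primary and secondary endpoints.** Quality of life, fatigue and pain relief are secondary. The primary endpoint is CTCAE toxicity at 3 months.
- **Statistical analysis and randomization.** Longitudinal variables are handled as follows: "Additionally, for variables with longitudinal measurements, the time courses of individual patients will be analyzed and summarized by treatment groups". Descriptive p values will come from tests between the groups, which are not named. The Wilcoxon signed rank test is to be "used to compare changes in group difference". Cohen's effect size is to be computed for change in the questionnaire measures. No baseline covariate or regression model is mentioned.

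**The concern.** A raw change score subtracts the whole baseline value, which fixes the slope on baseline at 1. With equal SDs at both times the best-fitting slope is the correlation rho, which is below 1. Subtracting the full baseline therefore adds noise. In a single small trial it also over-corrects a chance baseline difference between the groups. Randomization is described as blocked, with no mention of stratification by baseline pain or quality of life, so at about 30 per group some chance imbalance is plausible.

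At stake is the precision of the quality-of-life, fatigue and pain comparisons. Better quality of life is part of the trial's stated rationale, and a pilot of this size has little precision to spare. The t0 score needed to recover it is already being collected.

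**Working it through.** **The plan's own figure.** The article claims that "with a scheduled number of 30 patients per group" it can detect a Cohen's d "of 0.8 with a power of 80% and an alpha significance level of 5" per cent. Sidedness is not stated; two-sided is assumed. The normal approximation gives n = 2(1.960 + 0.842)²/0.8² = 24.5, so 25 per group. The exact t test needs 26. At 30 per group the power is 86% and d = 0.74 is detectable at 80% power. The stated figure errs on the safe side, and the present point does not change it.

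**Inputs for the comparison.**
- n = 30 per group, from the article.
- rho, the correlation between the t0 and follow-up scores: not given; assumed 0.3 to 0.7.
- SDs at t0 and follow-up: not given; assumed equal and set to 1.
- Dropout: no rate given; 30 evaluable per group assumed, with 20 as a sensitivity case.
- Comparator: a two-group comparison of change scores, which is the likely intention but is not spelled out.

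**Formulas.** The variance of the between-group difference is proportional to:
- change score: 2(1 − rho)
- ANCOVA, large samples: 1 − rho²
- ratio: (1 − rho²)/[2(1 − rho)] = (1 + rho)/2
- ANCOVA at n per group, charging for the estimated slope: multiply by 1 + 1/(2n − 4). At n = 30 this is 1 + 1/56 = 1.018.

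| rho | change | ANCOVA | ratio | ratio at n = 30 | SE smaller by | equivalent n per group by change | detectable difference (SD units, 80% power), change → ANCOVA |
|---|---|---|---|---|---|---|---|
| 0.3 | 1.40 | 0.91 | 0.65 | 0.66 | 19% | 45 | 0.87 → 0.71 |
| 0.5 | 1.00 | 0.75 | 0.75 | 0.76 | 13% | 39 | 0.74 → 0.64 |
| 0.7 | 0.60 | 0.51 | 0.85 | 0.87 | 7% | 35 | 0.57 → 0.53 |

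The equivalent n is 30 divided by the n = 30 ratio before rounding: 30/0.662, 30/0.763 and 30/0.865.

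**Sensitivity.**
- With 20 evaluable per group the ratios are 0.67, 0.77 and 0.87.
- Break-even at n = 30 is where (1 + rho)/2 × 57/56 = 1, that is rho = 112/57 − 1 = 0.965.
- With unequal SDs s0 (baseline) and s1 (follow-up), the change-score variance exceeds the large-sample ANCOVA variance by (s0² + s1² − 2·rho·s0·s1) − s1²(1 − rho²) = (s0 − rho·s1)², which is never negative. The gain shrinks as s1/s0 approaches 1/rho (1.43 at rho = 0.7, 2 at 0.5) and is zero there.

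**Simulation.** Normal data, 30 per group, true difference 0.6 SD, 4,000 runs per setting. Power:

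| rho | rank-sum on change | t test on change | ANCOVA |
|---|---|---|---|
| 0.3 | 46% | 49% | 66% |
| 0.5 | 60% | 63% | 74% |
| 0.7 | 83% | 85% | 89% |

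With no true difference the rejection rates lay between 4.5% and 6.0% across all methods and settings.

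**The case against.** The strongest reply is that this is a condensed article. A baseline covariate for a secondary outcome is commonly left to the analysis plan, which is not shown and may contain one. That would settle the matter if the article were silent on method. It is not: it names analyses for change, and those have no baseline term. What stands is that adjustment is nowhere excluded.

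Several stronger readings are tempting but not supported:
- *The plan commits to unadjusted between-group change.* The between-group tests are unnamed, the phrase about changes in group difference is unclear, and the Wilcoxon sentence is not tied to the questionnaires. This is the likely reading only. The sentence on time courses does not show the problem by itself, since it is compatible with a longitudinal analysis.
- *Each visit is tested separately, wasting the repeated measures.* The text does not say so.
- *The planned comparison is biased.* A change score uses t0 and is unbiased under randomization.
- *Adjustment is free.* It costs one degree of freedom and a modelling assumption.
- *A mixed model would gain more still.* The calculation covers a single follow-up visit only.

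It is also fair that the gain is modest at the upper end: at rho = 0.7 the SE falls by 7%, and simulated power is 89% against 85% for a t test on change. The formula is for mean-based analyses, whereas the test named is rank-based; the simulated rank-sum test on change nevertheless falls short of ANCOVA at each correlation tried.

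**Conclusion.** The point holds as an avoidable loss of precision in secondary, exploratory outcomes. Assuming rho between 0.3 and 0.7, equal SDs and 30 evaluable per group, ANCOVA has about 0.66 to 0.87 of the variance of a two-group change-score comparison. Both the correlation and the SD assumption come from outside the article, so only this range can be claimed.

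A reader might infer that the trial's main conclusion is at risk. It is not: the CTCAE primary endpoint and the sample-size statement are unaffected, and the p values are declared descriptive. Separately, and more seriously, the signed rank test is a paired test and cannot compare two independent groups. That defect stands whether or not baseline is adjusted for.

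**What to change.** For each BM22 and FA13 scale and for VAS pain, replace the sentence on the Wilcoxon test with an ANCOVA of the 3-month value (and likewise the 6-month value) on treatment, with the t0 score as covariate. Report A minus B with a 95% confidence interval. Cohen's effect size can stay as a descriptive addition. For skewed scales, add a rank-based ANCOVA or a between-group rank-sum test as sensitivity analysis. A repeated-measures model with the t0 covariate is an option. If the team prefers to report change, regressing change on treatment and t0 gives the same treatment estimate.

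The cost is a few lines of analysis text and SAS code, one degree of freedom (about 1.8% of variance at 30 per group) and the assumption of a common linear slope on baseline. No new patients, visits or data are needed. The article reports recruitment as incomplete, so at that stage the change could still be fixed before the final data. The same rewrite removes the paired test from the between-group comparison.
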